#### Statistical analysis

Statistical analysis will be conducted on the intention-to-treat population using Stata software, V.13 (StataCorp, College Station, Texas, USA). A two-sided P value of less than 0.05 will be considered for statistical significance. Baseline characteristics will be presented for each randomized group as the mean ± standard deviation or median (interquartile range) according to the statistical distribution for continuous data, and as the number of patients and associated percentages for categorical parameters. Comparisons between randomized groups will be analyzed using the Chi2 or Fisher’s exact test for categorical variables and the Student t-test or Mann-Whitney’s test for quantitative parameters, with normality verified by the Shapiro-Wilk test and homoscedasticity by the Fisher-Snedecor test (notably for primary outcome QUICK DASH scale at 3 months). Primary analysis will be completed using (1) ancova taking into account baseline QUICK DASH as covariate as recommended by Vickers and Altman [29] and (2) linear regression model in multivariate context. Covariates used for adjustment will be fixed according to (i) univariate results and (ii) clinical relevance including (use of analgesics) stratification factors. Results will be expressed as effect sizes and 95% confidence intervals. Regarding the analysis of repeated measures, random-effect models (linear or generalized linear according to the statistical distribution of dependent variables) will be performed, as usually proposed, to study the fixed-effects group, time points, and “group x time” interaction, taking into account between- and within-subject variability. The impact of covariates (as observance) will be also studied. A sensitivity analysis will be performed to study the impact of missing data; when appropriate, they will be handled in accordance with the estimation method developed by Verbeke and Molenberghs [30].

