### Instruments

The primary endpoint is the score on the Quick DASH scale at 3 months. The Quick DASH (Disability of Arm-Shoulder-Hand) is a self-administered questionnaire which measures the physical disability and symptoms for all upper limb disorders in an heterogeneous population and for acute as well as chronic disorders [22]. It contains various domains such as handicap, activity of daily living, pain during activities, strength. It has good psychometric properties with a Cronbach’s alpha coefficient of 0.89 and an intra-class correlation coefficient of 0.94 which suggests excellent test-retest reliability. We assessed functional capacity monthly over 6 months.

Secondary endpoints are:The areas of pain and intensity of the discomfort or pain are assessed using the Nordic questionnaire [21] and a numerical pain scale.Overall psychological status is assessed using the Hospital Anxiety and Depression Scale by Zigmond and Snaith [23].The SF-36 questionnaire is used for patient quality of life [24].Duration of sick leave accumulated during the study period.Use of analgesics.

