### Research design

A prospective, multicenter, comparative (one intervention arm vs. one control arm), randomized (immediate vs. later treatment) study using Zelen’s design [25]. Workers randomized to the intervention group will be given a short, intensive, standardized spa therapy treatment during the following month. The intervention will be offered to control-group subjects at least 3 months later. The total duration of participation in the study for patients is 6 months. The centers were Clermont-Ferrand University Hospital/Royat spa center, Nîmes and Montpellier Hospital/Balaruc spa center.

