### Randomization

The randomization list will be drawn up by the methodologist in charge of the project before the beginning of the trial. Randomization will be conducted so as to balance group numbers using block randomization stratified by center; this will make it possible to check patient eligibility and to communicate information on randomization to the investigator and any other correspondents for each of the workers.

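### Randomisation is stratified by centre, but the month-3 Quick DASH test has no centre term and the ANCOVA names only baseline; if centre predicts outcome, the unadjusted test is mildly conservative

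*Protocol article*

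**What the plan says.** The Randomization section of the protocol article states: "Randomization will be conducted so as to balance group numbers using block randomization stratified by center". Under Research design the sites are listed: "The centers were Clermont-Ferrand University Hospital/Royat spa center, Nîmes and Montpellier Hospital/Balaruc spa center". The number of strata is not given outright; two or three are compatible with that list.

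The Instruments section fixes the endpoint: "The primary endpoint is the score on the Quick DASH scale at 3 months". The Statistical analysis section compares the arms by "the Student t-test or Mann-Whitney’s test for quantitative parameters" and points expressly to the month-3 Quick DASH score as a case for this comparison. It then completes the primary analysis in two ways. The first is an "ancova taking into account baseline QUICK DASH as covariate"; the second is a multivariable linear regression. The next sentence reads: "Covariates used for adjustment will be fixed according to (i) univariate results and (ii) clinical relevance including (use of analgesics) stratification factors". This is the only place in the analysis text where the stratification factor comes in.

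**The concern.** Blocking within centre forces the arms to be nearly equal in size at each centre. Differences in outcome level between centres then largely drop out of the treatment difference. A two-group test that ignores centre still counts those differences as residual noise. Its standard error therefore describes a less precise design than the one used, and precision bought by the stratification is given away.

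The article states the test and the ANCOVA covariate explicitly, and centre is in neither. The one sentence that mentions stratification factors also allows covariates to be chosen from univariate results, and it does not say which of the two models it governs. A reader cannot tell whether centre is certain to be in any given model of the primary endpoint.

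A centre effect is plausible but not documented. The hospitals work with two different spa centres, and recruitment is local, through occupational health services and general practitioners.

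**Working it through.** **Inputs from the article (Sample size determination).** Two-sided 5% type I error, 90% power, SD 18, difference 12 points, 20% loss to follow-up, 75 randomised per arm.

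**The plan's own figure.** n per arm = 2 × 18² × (1.960 + 1.282)² / 12² = 47.3, rounded up to 48 evaluable; 48 / 0.80 = 60 randomised. The stated 75 is not reproduced from the printed inputs. The article also allows for a Hawthorne effect without quantifying it, and 75 is compatible with such an allowance: 75 × 0.80 = 60 evaluable, which gives 90% power for about 10.65 points. That difference is a separate matter. The working below takes the 60 evaluable per arm that the plan leaves.

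**Assumption.** R² is the share of month-3 outcome variance explained by centre. The article gives no figure, so a range of 0 to 20% is shown.

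**Formulas, with arms balanced within centre.**
- Standard error reported by the unadjusted t-test: 18 × √(2/60) = 3.29 (mean 3.28 in simulation).
- Standard error with centre in the model: 3.29 × √(1 − R²).
- Ratio of the two: 1/√(1 − R²).
- Actual type I error of the unadjusted test: 2 × [1 − Φ(1.96/√(1 − R²))].
- Power without centre for difference d: Φ(d/SE_adj − 1.96/√(1 − R²)). With centre: Φ(d/SE_adj − 1.96). SE_adj is the standard error with centre.

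Example, R² = 10%: SE_adj = 3.29 × 0.949 = 3.12; ratio 1.054; type I error 2 × [1 − Φ(2.066)] = 3.9%. For 12 points, power without centre is Φ(3.849 − 2.066) = 96.3%, and with centre Φ(3.849 − 1.960) = 97.1%.

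**Results.** The standard errors are simulation means (20,000 runs per setting, three equal centres, 60 per arm). The other columns are from the formulas.

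| R² (assumed) | SE without / with centre | Ratio | Type I error without centre | Power, 12 points, without / with | Power, 10.65 points, without / with |
|---|---|---|---|---|---|
| 0 | 3.28 / 3.28 | 1.000 | 5.0% | 95.5% / 95.5% | 90.0% / 90.0% |
| 5% | 3.28 / 3.19 | 1.026 | 4.4% | 95.9% / 96.3% | 90.6% / 91.4% |
| 10% | 3.28 / 3.11 | 1.054 | 3.9% | 96.3% / 97.1% | 91.1% / 92.7% |
| 20% | 3.28 / 2.93 | 1.118 | 2.8% | 97.1% / 98.3% | 92.4% / 95.2% |

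**Simulation check on type I error.** At R² of 0, 5%, 10% and 20%, the test without centre gave 5.0%, 4.6%, 3.6% and 2.9%; with centre it gave 5.0%, 5.2%, 4.8% and 5.0%. Blocks balance the 75 randomised, not the 60 analysed. When 20% were lost at random, the unadjusted test gave 4.4%, 4.0% and 3.3% at 5%, 10% and 20%, so imperfect balance softens the effect slightly.

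These figures are for the t-test. Neither the Mann-Whitney test nor an ANCOVA with a baseline covariate was simulated.

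**The case against.** The strongest reply is that centre is already in the plan. The covariate sentence brings stratification factors into at least one adjusted analysis of the primary endpoint. It follows both completing models, so it may cover the ANCOVA as well, and it places the stratification factors under clinical relevance rather than under univariate results. This stands in part: it would be wrong to say that centre is absent from the analysis. But the sentence does not change the t-test or Mann-Whitney comparison, and it leaves open whether centre is fixed in the ANCOVA.

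A second reply is that the loss is small and one-sided. This stands. There is no bias and no excess of false positives, and at 5% of variance the standard error is less than 3% too large. In the ANCOVA the gain may be smaller still, because baseline Quick DASH can absorb centre differences that come from case mix.

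A reader might extend the point to the repeated-measures models, which are described as serving "to study the fixed-effects group, time points, and “group x time” interaction, taking into account between- and within-subject variability". The article does not support that. A centre offset that is constant over time cancels from the group-by-time interaction. In a simulation of change scores (three centres, 60 per arm), with offset variance 0 or 20% of 18², type I error was 5.1% and 5.0% and the standard error was 2.58 in both. The text also leaves further covariates in those models open. Nor is the lack of centre-stratified versions of the secondary tests a finding, since that is ordinary analysis-plan detail which a condensed article may omit.

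**Conclusion.** The point holds as a modest, conditional one. The design stratum is missing from the headline month-3 test and from the stated ANCOVA covariates, and its only mention is worded loosely enough to leave its inclusion unsettled.

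One might infer that the standard errors are too large as a matter of fact. The article does not show that: it is true only if centre predicts month-3 Quick DASH, and no between-centre variance is given. If centre explains 5% to 20% of variance, the nominal 5% t-test runs at about 4.4% down to about 3%, and including centre would add 0.4 to 1.2 percentage points of power for 12 points at 60 evaluable per arm. For the smaller 10.65-point difference the gain is 0.8 to 2.8 points. With no centre effect, nothing is gained or lost. These figures rest on SD 18, equal centres, near balance within centre among those analysed, and no baseline adjustment.

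**What to change.** In the Statistical analysis section, specify the month-3 ANCOVA as Quick DASH on randomised group, baseline Quick DASH and centre as defined for the randomisation. Enter centre as a fixed effect and keep it whatever the univariate results. Word the covariate sentence so that data-driven selection cannot apply to centre. If the unadjusted test is retained, it should be read as conservative where centres differ.

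The cost is a change of wording before database lock and 1 or 2 degrees of freedom, depending on whether there are two or three strata. No new data are needed, because centre is already recorded for the randomisation.

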### Study objectives

This study falls under active UE-MSD prevention. Its primary aim is to show the superiority at 3 months of a combination of spa therapy, exercise, and self-management training for 6 days over usual care in the management of MSDs in terms of employee functional capacity in personal and professional daily life.

Secondary aims are to assess the benefit of the intervention in terms of pain, quality of life, and accumulated duration of sick leave.

This may lead to the possibility of proposing an alternative to conventional MSD treatment. The objective is to keep employees in work; the study design does not require sick leave. Decreased long-term use of analgesics is expected as well as a control of the unfavorable course of the MSDs. A resurgence in pain and fatigue immediately after the week of treatment is expected to be a possibility.

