### Sample size determination

To study the impact at 3 months of the 6-day standardized short thermal intervention on pain-related functional impairment measured using QUICK DASH scale (disability/symptom section), the sample size estimation is based on a comparison between both arms for a two-sided type-I error of 5 and 90% statistical power. According to the literature [26], it seems relevant to consider a standard deviation at 18 and a baseline value equaling 48 (/100) for the QUICK DASH scale. Considering (i) an assumed 25% improvement (−12 points) in favor of the 6-day standardized short thermal group, (ii) a possible Hawthorne effect (in the “delayed treatment” group), and (iii) a lost-to-follow-up rate of 20%, it is planned to include 75 patients per randomization group. Data will be entered in real time using the online clinical research data management tool REDcap (Research Electronic Data Capture). Assessment questionnaires will be data-scanned to prevent data entry risks.

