The various people in charge of the spa therapy who are responsible for conducting the intervention in this study, have more than 3 years of clinical experience and have been specifically trained in implementing the protocols by means of a detailed handbook that precisely describes each intervention illustrated with photographs and diagrams from the video program given to workers [27].

During the inclusion visit, control-group workers will be given the same folder as the intervention group, with the seven exercise sheets and USB key. The workers are not given guidance on the performance of any exercise that may have been determined by the conduct of the clinical examination. They will perform home program (exercises and relaxation) during the first three months and then the spa therapy of 6 consecutive days identical to the intervention group.

Intervention and control-groups workers will receive unrestricted pharmacological or non-pharmacological usual care from their physicians or specialists, such as analgesics, physiotherapy or orthosis, over 6 months. However, any medication taken during or after the intervention must be declared and reported in the patient follow-up questionnaires.

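### The supporting multivariable regression picks covariates from univariate results and names analgesic use without limiting it to a baseline value, so a post-randomisation outcome can enter the treatment-effect model

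*Protocol article*

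**What the plan says.** All references are to the protocol article.

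- **Statistical analysis.** QuickDASH at 3 months is compared between arms by t-test or Mann-Whitney test in the intention-to-treat population. Two models supplement this: an ANCOVA on baseline QuickDASH and a multivariable linear regression. The covariate rule reads: "Covariates used for adjustment will be fixed according to (i) univariate results and (ii) clinical relevance including (use of analgesics) stratification factors". After the repeated-measures models the section adds: "The impact of covariates (as observance) will be also studied".
- **Instruments.** The last secondary endpoint listed is "Use of analgesics".
- **Study objectives.** "Decreased long-term use of analgesics is expected".
- **Intervention protocol.** Both arms may receive analgesics as usual care for 6 months, and "any medication taken during or after the intervention must be declared and reported in the patient follow-up questionnaires".
- **Randomization.** The list uses "block randomization stratified by center"; no other stratification factor is named.

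**The concern.** A covariate may safely adjust a randomised comparison if allocation cannot have changed it. Analgesic use at inclusion meets that condition. Analgesic use during follow-up does not: the protocol itself expects the programme to reduce long-term use and counts use as an outcome. With follow-up use in the model, the group coefficient compares workers with the same follow-up analgesic use. That is a different question from the effect of being randomised to the programme, and it has no simple causal reading when severity drives both use and score.

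The rule also leaves the remaining covariates to univariate results, so the model is unknown until outcome data have been examined. Workers, physicians and assessors are described as impossible to blind, although the same section also says the primary endpoint was evaluated blind. An open model choice is therefore better avoided. The practical risk is an adjusted estimate that disagrees with the two-group test for an artificial reason, with no rule fixed beforehand for explaining it.

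**Working it through.** **1. Can the text admit follow-up use?** The covariate rule gives no time of measurement. The only collection of medication data that the article describes is during or after the intervention. The inclusion-visit list (Procedure for data collection) covers sociodemographic and job data and does not mention analgesics. The questionnaire schedule is in Fig. 2, which is not shown. So the text permits follow-up use but does not state it.

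**2. Inputs from the plan.** Sample size determination gives a "two-sided type-I error of 5 and 90% statistical power", "a standard deviation at 18 and a baseline value equaling 48 (/100) for the QUICK DASH scale", a 12-point difference, 20% loss to follow-up and 75 per group.

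- Plan's own figure: n = 2 × (1.960 + 1.282)² × (18/12)² = 47.3, so 48 per arm; 48/0.8 = 60. The stated 75 also contains a Hawthorne allowance with no figure. A net difference of about 10.7 points gives 60/0.8 = 75, so 75 is not shown to be wrong, and this point does not depend on it.
- Completers: 75 × 0.8 = 60 per arm.
- Unadjusted: SE = 18 × √(2/60) = 3.29; power = Φ(12/3.29 − 1.96) = 0.955.

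**3. Effect of adjusting for follow-up use.** Let *a* be the fall in the proportion using analgesics caused by treatment, and *b* the QuickDASH points by which users exceed non-users within an arm. The adjusted coefficient is then

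adjusted effect = 12 − a × b.

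The documents give neither *a* nor *b*, nor the level of use. All are assumed, with 60% use in controls.

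| a | b | adjusted effect | change | power, 60 per arm |
|---|---|---|---|---|
| 0 | any | 12.0 | none | at least 0.955 |
| 0.1 | 5 | 11.5 | 4% lost | 0.94 |
| 0.2 | 10 | 10.0 | 17% lost | 0.87 |
| 0.3 | 15 | 7.5 | 38% lost | 0.66 |
| 0.1 | −5 | 12.5 | 4% gained | 0.97 |

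Power uses residual SD √(18² − b²v), where v is the mean within-arm variance of use, and divides the SE by √(1 − r²), where r is the correlation of use with arm. For a = 0.2, b = 10: v = 0.24, residual SD 17.3, r = 0.2, SE = 3.23, power = Φ(10/3.23 − 1.96) = 0.87. The last row shows the other direction: if users score lower because the drug works, adjustment enlarges the estimate.

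**4. Simulation checks (60 per arm, true effect 12).**

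- a = 0.2, b = 10: adjusted estimate 10.0, as the formula gives.
- Same values, with an unmeasured severity factor driving both use and score (loading 0.5, residual SD 14): 8.8. With a = 0.3, b = 10: 7.2, about 40% lost, slightly beyond the table.
- Use generated from the month-3 score itself, P(use) = logistic((score − 45)/12): 54% of controls and 37% of intervention workers use analgesics, and the adjusted estimate is about 8.6, 28% lost. Users then score about 21 points worse than non-users, more than one SD. With scale 40 instead of 12, the estimate is 11.4, 5% lost.
- Use driven by baseline severity only: 12.0, no loss.

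**5. Univariate selection alone.** Selecting among 5 to 20 simulated baseline covariates at p < 0.05 or p < 0.20 gave type I error of 0.045 to 0.054. With 4,000 runs the simulation error is √(0.05 × 0.95/4000) = 0.003, so there is no visible inflation.

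**The case against.** The strongest reply is that the rule can be read benignly. It does not say that follow-up use is meant. The medication sentence in Intervention protocol is a reporting requirement and does not show that use goes unrecorded at inclusion. The inclusion-visit list omits baseline QuickDASH too, although the ANCOVA needs it, so its silence on analgesics proves little. The reference to stratification factors can be read as a second item (centre), not as a claim that analgesic use was a stratifier. All of this stands, and it makes the defect a rule that admits a harmful covariate, not a stated decision to use one.

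Four stronger readings are tempting, and the documents do not support them:

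- *The primary result is biased.* Only the multivariable regression is touched. The two-group test and the ANCOVA on baseline QuickDASH still estimate the effect of randomisation.
- *Adjustment necessarily removes part of the effect.* The direction depends on whether users score worse or better. The stated expectation concerns long-term use, while the endpoint is at 3 months.
- *Univariate selection invalidates the p-value.* The check showed no inflation for baseline covariates. The complaint is that the model is not fixed in advance.
- *Observance is adjusted for in the primary comparison.* The text says only that its impact will be studied, alongside the repeated-measures models.

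It may also be said that a final covariate list belongs in the statistical analysis plan. That would answer mere silence, but the article states a selection rule, and the rule itself is the problem.

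**Conclusion.** The point holds as a should-fix. The article sets a data-driven covariate rule and names a variable that it treats elsewhere as an outcome, without confining it to a baseline value. If follow-up use is entered, the regression coefficient is not the intention-to-treat effect. For a 12-point effect, the illustrated loss runs from none to about 38%, slightly more in one scenario with shared severity, and a gain is possible if analgesics lower the score. These sizes rest entirely on assumed rates of use and assumed links between use and score. If only use at inclusion, recorded before allocation, is entered, there is no bias and only the lack of pre-specification remains.

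**What to change.** Replace the covariate rule in Statistical analysis with a fixed list of baseline variables: baseline QuickDASH, centre (the one stratification factor) and, only if recorded before allocation, analgesic use at inclusion. Delete univariate results as a selection criterion. State that follow-up analgesic use is analysed only as the secondary endpoint it already is. State that analyses of observance are exploratory and separate from the treatment-effect estimate.

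The cost is a few sentences in the analysis section, with no change to sample size, visits or the main comparison. If use at inclusion is wanted as a covariate and is not yet recorded, it needs one question at the inclusion visit, answered before allocation.

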### Selection criteria

#### Inclusion criteria

Participants are workers with latent or symptomatic MSDs according to the SALTSA European consensus/INRS (French occupational health and safety agency) [20] with a value on the Nordic questionnaire strictly above 2/10 [21]. They are aged between 18 and 65 years, have or have not a history of sick leave, and are covered under national health insurance. No restriction was made regarding type of job or workstation.

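### Own-baseline adjustment is written down only for Quick DASH; as written, pain and quality-of-life comparisons are unadjusted or change-score contrasts, both less precise than adjusting for baseline

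*Protocol article*

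**What the plan says.** All of the analysis text is in the Statistical analysis section of the protocol article. It has four relevant parts.

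- **General comparison.** Quantitative parameters are compared between randomised groups by Student's t-test or Mann-Whitney. Quick DASH at 3 months is singled out as a notable case, so the rule is not confined to it.
- **Primary score.** "Primary analysis will be completed using (1) ancova taking into account baseline QUICK DASH as covariate", followed by a multivariable linear regression. The next sentence says that covariates are chosen on univariate results and clinical relevance, and it mentions stratification factors. It names no outcome.
- **Repeated measures.** The plan here reads: "random-effect models (linear or generalized linear according to the statistical distribution of dependent variables) will be performed, as usually proposed, to study the fixed-effects group,". The other fixed effects listed are the time points and the group-by-time interaction.
- **Further covariates.** Their impact will also be studied. The one example given is observance, which is measured after randomisation.

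Elsewhere, entry requires SALTSA-defined disease "with a value on the Nordic questionnaire strictly above 2/10" (Inclusion criteria), and among the secondary endpoints "The areas of pain and intensity of the discomfort or pain are assessed using the Nordic questionnaire" (Instruments). Allocation uses "block randomization stratified by center" (Randomization). Pain and quality of life are stated secondary aims (Study objectives).

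**The concern.** The plan accepts the case for baseline adjustment, citing a methodological source for it, but writes it down for one score. The methods it states for pain, anxiety and depression, and SF-36 contain neither the score's own baseline value nor the factor on which randomisation is stratified.

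At least one of those baselines is certain to exist, because a Nordic value is needed to enter the trial.

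At stake is the precision of the secondary comparisons. Intervals for pain and quality of life would be wider than the collected data require. If the comparison is purely post-treatment, a chance baseline imbalance between two arms of about 60 also carries into it. Month 3 is the visit that matters most, because controls are offered the spa course from 3 months onward (Research design).

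**Working it through.** **The plan's own figure.** The inputs are in Sample size determination: "the sample size estimation is based on a comparison between both arms for a two-sided type-I error of 5 and 90% statistical power", "it seems relevant to consider a standard deviation at 18 and a baseline value equaling 48 (/100) for the QUICK DASH scale" and "an assumed 25% improvement (−12 points) in favor of the 6-day standardized short thermal group". The normal-approximation formula gives

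n = 2 × (1.960 + 1.282)² × 18² / 12² ≈ 47.3, so 48 per arm.

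Allowing for 20% loss, 48 / 0.80 = 60 randomised per arm, against 75 planned. The section also names a Hawthorne allowance without giving its size. Sixty evaluable per arm have 90% power for 10.65 points, so an allowance of about 1.3 points would account for 75. An input is missing, so 75 is not shown to be wrong. It is used here only for the evaluable number: 75 × 0.80 = 60 per arm.

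The article gives no standard deviation, effect size, power or baseline-to-follow-up correlation for any secondary score. What follows is therefore on a standardised scale, with the correlation r assumed between 0.3 and 0.7.

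**Variance of the month-3 group difference, relative to an unadjusted comparison** (equal variances at both visits, one follow-up visit):

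- unadjusted: 1
- change score, which is the group-by-time contrast when baseline enters as an unconstrained time point: 2(1 − r)
- baseline as covariate: 1 − r²

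The ratio of the last to the second is (1 − r²) / [2(1 − r)] = (1 + r)/2, which is below 1 whenever r < 1. The change score is worse than no adjustment when 2(1 − r) > 1, that is, when r < 0.5.

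**Power.** Two-sample non-central t, 60 per arm, two-sided 5%. The standardised effect with 80% unadjusted power is d = 0.516. It is divided by √(1 − r²) for baseline adjustment and by √[2(1 − r)] for the change score.

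| Assumed r | Variance, adjusted | Variance, change score | Power, unadjusted | Power, change score | Power, adjusted |
|---|---|---|---|---|---|
| 0.3 | 0.91 | 1.40 | 80% | 65.8% | 83.6% |
| 0.5 | 0.75 | 1.00 | 80% | 80.0% | 89.9% |
| 0.7 | 0.51 | 0.60 | 80% | 95.1% | 97.5% |

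At r = 0.5, adjustment is worth 60 / 0.75 = 80 evaluable per arm instead of 60. For an effect with 90% unadjusted power (d = 0.597), adjustment at r = 0.5 gives 96.3%.

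**Centre.** The article gives no share of variance due to centre. If it were 1%, 5% or 10%, including centre would move 80% power to about 80.4%, 82.0% or 84.0%. These are illustrations only, and no quantified gain from centre is claimed.

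**The case against.** The strongest objection is that the article nowhere says secondary scores are analysed without baseline or centre. A reader might infer that they are, but the text does not support that.

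- The covariate sentence names no outcome, and it does mention stratification factors.
- The effects listed for the random-effect model may be those of interest, not a closed list.
- The sentence on the impact of covariates is open-ended.
- Baseline may be one of the time points. The questionnaire schedule is in Fig. 2, which is not shown. If baseline is a time point, a change contrast subtracts it, and an imbalance does not pass straight into the comparison.
- The article condenses a fuller protocol, and an analysis plan may settle the matter.

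This limits how firmly the point can be put. It does not remove it, because the section does state methods for these scores, and the kinder reading (baseline as a time point) still leaves a change score. Only a model that constrains the arms to a common baseline mean would recover the precision of ANCOVA, and the text mentions no such constraint.

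Three further objections stand:

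- Collection of the anxiety and depression scale and SF-36 at entry is not visible in the text. Only the Nordic value is.
- The entry threshold truncates baseline Nordic pain and may lower its correlation with follow-up, which would shrink the gain over an unadjusted test.
- At r = 0.7 the gain over a change score is only about 2 points of power (95.1% to 97.5%).

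**Conclusion.** The point holds in limited form. Own-baseline adjustment is explicitly assigned only to Quick DASH, and the methods stated for the other continuous scores are less precise than adjusting for baseline, whether or not baseline is a time point.

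If those comparisons are unadjusted, the gain ranges from about 4 points of power at r = 0.3 to about 17 at r = 0.7, starting from 80%. If they are change scores, it ranges from about 18 points at r = 0.3 to about 2 at r = 0.7. All of this rests on an assumed correlation, 60 evaluable workers per arm and equal variances. The article supplies only the 75 and the 20% behind the 60.

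This concerns the precision of secondary aims. In a randomised comparison it is not a source of systematic bias, and it leaves the primary result untouched.

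**What to change.** In the Statistical analysis section, state that each continuous secondary score collected at entry (at least the Nordic pain score) is analysed in the random-effect model already planned, with two additions: its own baseline value as a covariate, and centre as the stratification factor. Report the adjusted month-3 group difference with its 95% CI. Keep the t-test or Mann-Whitney comparison of these scores as descriptive. A baseline-by-time term is optional.

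If the full protocol or analysis plan already specifies this, a sentence in the section saying so is enough.

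The cost is wording and a few degrees of freedom. For scores collected at entry, no extra workers, visits or data are needed.
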